### Objectives

This study aims to determine the effectiveness of topical silicone gel versus pressure garment therapy versus combined topical silicone gel and pressure garment therapy, in the prevention and management of burn scars in children aged 0 to16 years post burn or 0 to18 years post burn scar reconstruction. This will be investigated using the primary outcomes of scar itch and thickness at 6 months post burn or burn scar reconstruction. Current medical literature has been unable to demonstrate one treatment group as being superior to the others; however, we hypothesise that there will be at least one pairwise difference between the group means for scar thickness at the 6-month endpoint.

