## Methods

### Study design

A randomised controlled trial with three parallel arms will be conducted to examine the effectiveness of Strataderm® topical silicone gel, pressure garment therapy, and combined topical silicone gel and pressure garment therapy for the prevention and management of burn scars in children. Individual randomisation by patient will be undertaken using computer-generated random numbers. Randomisation will occur using a 1:1:1 ratio between groups in blocks of 12 and will be stratified by surgical intervention received (i.e. skin grafting in the acute phase, spontaneous skin healing in the acute phase, post-acute reconstructive surgery). Concealment of treatment allocation will be completed by the use of sealed, opaque, identical and serially numbered envelopes prepared in advance by an independent party. All outcomes will be measured at baseline (scar intervention commencement), 3 months and 6 months post burn or reconstruction. The primary outcome measures and the level of pressure beneath pressure garments will also be measured at 1 week post baseline. This project has ethics approval from the Child Health Queensland Human Research Ethics Committee (HREC). A flow diagram of the data collection process is displayed in Fig. 1.

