### Statistics

#### Sample size

The sample size estimate was calculated based on the primary outcome of scar thickness at 6 months post burn for one scar site. We assumed a pooled standard deviation of 1.0 mm based on a retrospective audit of data from our centre. To detect a statistically significant between-group difference of 0.76 mm in scar thickness with 80% power and an alpha value of 0.017 (due to three pairwise comparisons), 36 participants are required in each of the three groups. Assuming a 20% dropout, the total number of participants who need to be recruited at baseline is 135 (45 participants per group).

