The primary outcomes will be analysed using mixed effects regression analyses to examine differences at 6 months post burn, adjusting for the baseline value of the outcomes. Mixed effect regression analyses will be completed for each follow-up time point. Potential confounding variables that are identified as imbalanced between the groups will be entered into regression analyses. The time-varying covariates are patient adherence, level of pressure beneath garments, and other interventions received. All of the other potential confounding variables are non-time-dependent covariates. Sensitivity analyses will be completed for missing data using multiple imputation of missing observations by creating ten complete data sets [49] of missing dependent and independent data. For participants from whom data is collected from two scar sites, the multiple sites on these individuals will be accounted for in analytic models by including the scar site as a random effect nested within participant. Initially all participants will be included in the analyses. The analyses will then be repeated after stratifying by surgical intervention (i.e. skin grafting in the acute phase, spontaneous skin healing in the acute phase, post-acute reconstructive surgery). Subsequently, the influence of sociodemographic, clinical and intervention factors, and primary and secondary outcomes not included as dependent variables, on primary and secondary outcomes will also be examined using regression models. Differences in health-related quality of life between the intervention group and respective normative comparison groups will be analysed using *t* tests, z-scores, or equivalent nonparametric tests where appropriate. Differences in self-reported outcomes by children versus caregivers, between age groups and in comparison to normative data will also be examined using univariate statistics such as *t* tests, z-scores, or nonparametric equivalents. Significance will be set at less than 0.05. Data will be analysed using SPSS (SPSS Inc., Chicago, IL, USA) or Stata (StataCorp, College Station, TX, USA) where appropriate.

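### The trial is sized at alpha 0.017 for three pairwise comparisons but declares significance at 0.05, which gives a false-positive risk of about 12% on scar thickness alone

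*Protocol article*

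**What the plan says.** Three places in the protocol article bear on this point.

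- **Objectives.** The hypothesis is that "there will be at least one pairwise difference between the group means for scar thickness at the 6-month endpoint". No pair is singled out, so any of the three can establish it.
- **Sample size.** The calculation uses "an alpha value of 0.017 (due to three pairwise comparisons), 36 participants are required in each of the three groups". The target is a "between-group difference of 0.76 mm in scar thickness" with 80% power and a standard deviation of 1.0 mm.
- **Data analysis.** The section describes the mixed effects regression for the primary outcomes, the repeat analyses by surgical stratum and the secondary comparisons. The same paragraph then states: "Significance will be set at less than 0.05". No other threshold appears in the section. It does not carry 0.017 forward, and it gives no global test, order of testing or multiplicity adjustment.

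**The concern.** The two sections give different significance levels for the same three comparisons. The sample size section treats the comparisons as a family and protects it. The analysis section, read plainly, removes that protection.

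The form of the hypothesis makes this matter. When one significant pair out of three is enough, the relevant error rate is the chance that at least one of the three is falsely significant, and that rises well above 5% if each is judged at 0.05. A thickness p-value between 0.017 and 0.05 would be reported as a positive primary result under one section and a negative one under the other. The stated 80% power also belongs to a test at 0.017, which is not the test the analysis section describes. Leaving the choice until results are known is what pre-specification is meant to prevent.

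**Working it through.** **Inputs.** From the sample size section: difference 0.76 mm, SD 1.0 mm, power 80%, alpha 0.017, 36 evaluable per group, 20% dropout. From the study design section: 1:1:1 allocation. Sidedness is not stated, so two-sided tests are assumed.

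**1. Reproduce the plan's sample size.** The normal approximation is n per group = 2 × (z₁₋α/₂ + z₀.₈₀)² × SD² / difference².

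- Alpha 0.017: 2 × (2.387 + 0.842)² / 0.76² = 36.1, in line with the stated 36 (37 if rounded up; an exact t-test needs 38).
- Alpha 0.05: 2 × (1.960 + 0.842)² / 0.76² = 27.2, or 28 per group.
- One-sided alpha 0.017 gives 31, which does not match.
- Dropout: 36 / 0.8 = 45 per group, and 3 × 45 = 135, as stated.

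So two-sided 0.017 was really used, and it added about 8 evaluable children per arm (36 against 28).

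**2. Familywise error on thickness when the three arms are equal.** With pooled variance and 3 × 36 − 3 = 105 degrees of freedom, the chance that at least one of three pairwise t-tests is significant is P(Q > √2 × t_crit), where Q is the studentized range for three groups. This allows for the correlation between the three comparisons.

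| Level per comparison | t_crit (df 105) | √2 × t_crit | Chance of at least one false positive |
|---|---|---|---|
| 0.05 | 1.983 | 2.804 | 12.1% |
| 0.017 | 2.425 | 3.430 | 4.4% |

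Treating the comparisons as independent would overstate the first figure: 1 − 0.95³ = 14.3%.

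**3. Range of results on which the two sections disagree.** The standard error of a pairwise difference is 1.0 × √(2/36) = 0.236 mm. The smallest significant difference is 1.983 × 0.236 = 0.47 mm at 0.05 and 2.425 × 0.236 = 0.57 mm at 0.017. Observed differences between these values get opposite verdicts.

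**4. Power for a true 0.76 mm difference, 36 per arm, df 105.** It is 79% at 0.017 and 89% at 0.05.

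**5. A gated alternative.** Test the global three-group effect at 0.05 and, only if it is significant, test the pairs at 0.05. In simulation with 36 per arm, the familywise error was 5.0% both when all arms were equal and when two were equal and the third differed greatly. Power for the 0.76 mm pair was 81% to 87%, depending on where the third arm's mean lies between the other two.

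**6. Adding itch.** The protocol has two primary outcomes, so six comparisons are made at 6 months. The correlation between outcomes is not given. Assuming 0.8 down to 0, the chance of at least one false positive is about 18% to 23% with all six at 0.05, and about 7% to 9% with all six at 0.017.

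Steps 2 to 5 use simple comparisons of means. The planned mixed models, with baseline adjustment and up to two scar sites per child, would change the standard error in step 3 and the power. They would hardly change the familywise figures, which depend mainly on the number of groups and the threshold.

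**The case against.** The best defence is that the two levels fit together. Since 0.05/3 = 0.017, the 0.05 could be the overall level and 0.017 the per-comparison level already fixed by the sample size section. The 0.05 sentence follows the secondary t tests and z-scores and comes just before the software, so it may be routine wording never meant for the primary pairs. If 0.05 is a familywise level, or a global test comes first, the error on thickness stays near 5%. But the text says neither, and the sentence stands without exception in the paragraph that sets out the primary analysis. A plausible intention is not a stated rule.

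Other points stand, with limits:

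- **The 12% is conditional.** It applies when all three arms are equal and each pair is judged at 0.05. If one arm truly differs, only one true null comparison remains, with error of about 5%.
- **The mismatch does not leave the trial underpowered.** At 0.05 the power is higher than planned. The harm is to the error rate and to the clarity of the decision rule.
- **Correcting thickness alone does not settle itch.** This is right, and is a further matter for the authors. It does not remove the conflict on thickness.
- **A condensed article may leave multiplicity detail to an analysis plan.** That would excuse silence, but here two different levels are stated for the same comparisons.

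**Conclusion.** The concern holds. The protocol article sizes the trial at 0.017 per pairwise comparison and states 0.05 as its only decision threshold. Read as written, the risk of at least one false claim on 6-month thickness is 12.1%, against 4.4% at the level used for sizing. This assumes two-sided tests, 36 evaluable children per arm, no true difference between arms, and each pair judged at 0.05. It counts thickness only; the second primary outcome takes it to roughly 18% to 23% under the assumed range of correlations. Because the conflict concerns the primary claim and can reverse the conclusion for observed differences of about 0.47 to 0.57 mm, it must be resolved before the outcome data are analysed.

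**What to change.** Add to the data analysis section one of the following.

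- **Carry the design level forward.** Each of the three pairwise comparisons of thickness at 6 months is tested at two-sided 0.017 (0.05/3) and reported with a 98.3% confidence interval; 0.05 applies only to exploratory tests.
- **Gate the pairs.** The global three-group effect on thickness at 6 months (2 degrees of freedom) is tested at 0.05, and pairs are tested at 0.05 only if it is significant. With exactly three groups this holds the familywise error at 5%. It suits the stated hypothesis and gives somewhat more power than 0.017.

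The first option is sufficient and matches the existing sample size calculation. Either costs one or two sentences, with no extra patients and no change to the 135. The price is a stricter bar for p-values between 0.017 and 0.05, or the need to pass the global test.

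Both options cover thickness only. The same amendment should say how itch shares alpha with it, for example by ordering the two outcomes or dividing the level between them. Testing all six comparisons at 0.05/6 would hold the overall error at about 4% to 4.5%, but the sample size was not calculated for that stricter level.

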### Data storage

All information collected as part of this study will be stored safely in a locked filing cabinet in a locked office and in password-protected computer files. Any information obtained in connection with this research project that has the potential to reidentify participants will remain confidential and securely stored. The data collected from this study will be kept for 15 years, as per the recommendations of the National Health and Medical Research Council Guidelines (NHMRC).

## Discussion

Silicone products and pressure garment therapy have been accepted treatments for burn scar management in high-income countries for over 40 years, though there is minimal evidence to support their use [5, 7, 10, 13]. In addition, minimal research has been completed with a paediatric burns population or with any age group using a broad evaluation that investigates the effectiveness of scar prevention interventions, their impact on health-related quality of life, the burden of treatments on patients and their families, or the paediatric patient’s adherence to these interventions.

Whilst little is known about adherence to recommended wear and care regimes for children using topical silicone gel and/or pressure garments, adherence by children is likely less than optimal. In adults, adherence to recommended pressure garment therapy has recently been recorded as 15 to 80% with reasons for nonadherence including the cosmetic appearance of garments, insufficient education regarding garment use as well as poor fit and discomfort [50]. Low rates of adherence to recommended silicone gel sheeting use (24 h per day) have also been reported in adults [51]. It is expected that adherence will be greater when using topical silicone gel (Strataderm®) compared to pressure garment therapy due to its reduced application time and there being no need for additional care/maintenance of the product.

The burden of topical silicone gel also appears lower than pressure garment therapy due to recommended application of the product once or twice daily (depending on scar location), fast drying time and durability. However, topical silicone gels may be time-consuming to apply to an extensive body surface area and have been documented to cause local dermatological reactions [25]. Thus, further investigation of their effectiveness is required.

The burden of pressure garment therapy can be high for patients and their families due to prolonged recommended wearing time, 23 h per day until scar maturation [2, 5], and the need for regular replacement of garments. Pressure garments can also cause discomfort when they are ill-fitting, can instigate changes in bone growth, and can cause heat reactions and friction damage to new skin [2, 7]. In addition to these physical symptoms, pressure garments may also result in emotional and psychological reactions in children with burn scars through visible cosmetic differences, separate from the visible difference that may result from scarring [11].

### Significance of the study

This study will provide evidence of the effectiveness of three burn scar interventions for the prevention and management of burn scars in children. Specifically, evidence will be obtained regarding the effectiveness of topical silicone gel alone, pressure garment therapy alone, and a combination of topical silicone gel and pressure garment therapy. Future randomised control trials will be required to confirm these results; however, if consistent results are achieved, changes in clinical practice may occur.

By using a broad evaluation framework in combination with a design that carefully controls for confounding factors and investigates influencing factors, this study may determine which children benefit most from the scar management interventions of interest. Cost-effectiveness from a health service perspective will also be examined, which, to the knowledge of the authors, has not been examined in scar management intervention studies to date. Examining and controlling for the influence of a range of potential confounders will maximise the rigour of the study and will inform future studies of the factors that influence scar outcomes. Whilst this study will follow patients up to 6 months post burn, it study will pave the way for similar studies with follow-up to scar maturation (which can extend to 18 months post burn or longer) and multicentre trials.

## Trial status

Recruitment commenced at the end of August 2016 and it is expected that recruitment will take approximately 1 year to complete with final data collection occurring in February 2018.

## Abbreviations

CHU9D: Child Health Utility 9D
EQ5D-Y: EuroQol 5D - Youth
HREC: Human Research Ethics Committee
ICC: Intraclass correlation coefficient
ITT: Intention-to-treat
NHMRC: National Health and Medical Research Council Guidelines
NRS: Numeric rating scale
POSAS: Patient and Observer Scar Assessment Scale
RCT: Randomised controlled trial
TBSA: Total body surface area
